**1. Object and meaning**

In patients aged ≥80 years who will undergo elective surgery under general anesthesia, the incidence of hypotension during induction using remimazolam will be compared in a group using propofol as a control.

**2. Evidence of scientific rationality of research**

**2.1. Explanation of the target disease**

In Japan, the proportion of elderly people is increasing. Therefore, the number of surgeries for elderly patients will also increase. Because elderly patients tend to have a decline in physical and physiological functions and have more comorbidities, anesthetists must be managed more carefully than younger patients. According to a survey on the investigation of anesthesia-related complications in 2018 by the Japanese Society of Anesthesiologists, the frequency of cardiac arrest and severe hypotension began to increase in the in patients aged >80 years and was highest in patients aged >90 years except in the neonatal period <1 month. The frequency of hypotension during anesthesia is higher in the elderly than in other age groups, and increasing age is associated with a higher frequency of hypotension during the first 20 min after induction of general anesthesia. Hypotension during general anesthesia has been suggested to be associated with poor outcomes, such as organ dysfunction or perioperative mortality. Therefore, it is clinically meaningful to verify the occurrence of hypotension with remimazolam compared with controls, especially in the elderly. A reduction in the occurrence of hypotension is expected to provide better quality care to the elderly and reduce medical costs.

**2.2. Control treatment**

Propofol, which has a rapid onset and a few side effects, is one of the standard sedatives for induction of general anesthesia. However, propofol has some disadvantages, such as vasodilation or reduction in cardiac output. Age-related physiological and physical changes, such as autonomic nervous system dysfunction and arteriosclerosis, tend to cause propofol-induced hypotension, especially in older patients compared with other age groups. The package insert for propofol states that it should be used with caution in patients with American Society of Anesthesiologists (ASA) risk category III/IV and elderly patients and recommends slowing down the rate of administration to 1/2 of the usual dose, or 0.25 mg/kg/10 s.

**2.3. Trial treatment**

Remimazolam, approved for the induction and maintenance of general anesthesia or procedural sedation, is a full agonist at the benzodiazepine-binding site of the GABA A receptor. Remimazolam is a novel, short-acting drug because it is rapidly metabolized by nonspecific tissue esterases, and its metabolites have no drug activity. Remimazolam was noninferior to propofol in terms of efficacy as a hypnotic for general anesthesia. The incidence of hypotension that required treatment during general anesthesia in the remimazolam group tended to be lower than in the propofol group (33% vs. 60%). In a trial investigating the efficacy and safety of remimazolam collected in ASA PS of class III or higher, the incidence of decreased blood pressure throughout the trial period was 67.7% when remimazolam was administered at 12 mg/kg/h for induction. However, to our knowledge, no randomized controlled trials have examined the incidence of hypotension during general anesthesia induction using remimazolam in elderly patients as the primary outcome.

**2.4. Trial design and primary endpoints**

This is a single-center, double-blind, randomized, two-arm parallel-group, standard treatment-controlled, interventional clinical study.

Many factors are associated with the hemodynamic fluctuations caused by general anesthesia. We plan our study design as a prospective randomized control trial because the number of cases required to adjust all these factors based on observational studies is enormous. Due to the potential for arbitrary dropouts and preconceived evaluation of outcomes, a double-blind study design was adopted. Blinding of the patient is done to prevent the anesthetists and evaluator from breaking the blinding by unexpectedly vocalizing the drug name.

**Primary outcome:** The primary outcome will be the incidence of hypotension between the start of propofol or remimazolam and 3 min after tracheal intubation. Hypotension was defined as a mean arterial pressure <65 mmHg, as measured in the brachial artery using a manchette. Mean arterial pressure was selected as the primary outcome because a mean arterial pressure <65 mmHg sustained for more than 5 min during general anesthesia has been suggested to be associated with the occurrence of perioperative organ damage, such as cardiac and renal, and perioperative mortality.

**2.5. Significance of this study**

The proportion of elderly people in Japan is increasing. The demand for surgery for elderly patients is also increasing. Elderly patients tend to have a decline in physical and physiological functions and tend to have more comorbidities. Due to the high risk of perioperative complications, anesthesiologists should manage general anesthesia in elderly patients more carefully than in younger patients. Age-related physiological and physical changes tend to cause propofol-induced hypotension compared to other age groups, especially in older patients. Therefore, it is clinically meaningful to verify the occurrence of hypotension with remimazolam compared with controls, especially in the elderly. A reduction in the occurrence of hypotension is expected to provide better quality care to the elderly and reduce medical costs. If the results are negative, it indicates that there is little need to change the current clinical practice.

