**9.2. Calculation of sample size**

The frequency of hypotension associated with the induction of general anesthesia was estimated to be 40% based on cases similar to our protocol extracted from our institutional data for a randomly selected month. In a previous study, the relative risk of remimazolam to propofol for the frequency of hypotension associated with induction of anesthesia was reported to be 0.28. If Fisher’s exact probability test with a type I error set at 5% and a power greater than 80% will be performed, it was estimated that at least 84 participants per group would be needed. Considering a dropout, we decided to include 45 participants in each group (*i.e.*, 90 in total).

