**10.3. Anticipated AEs, etc.**

**Remimazolam:** In a study of Japanese patients who underwent surgery under general anesthesia, the incidence of adverse drug reactions in the remimazolam 12 mg/kg/h group was 42.7% (64/150 patients).

Major side effects: Hypotension 24.0% (36/150 cases), vomiting 7.3% (11/150 cases), nausea 6.7% (10/150 cases).

Serious side effects: Dependence (frequency unknown), bradycardia (4.7%), hypotension (26%), respiratory depression (frequency unknown), delayed arousal (frequency unknown), shock, anaphylaxis (frequency unknown).

Other side effects include: skin erythema (1−10%), headache (1−10%), delirium/dyskinesia (<1%), agitation (frequency unknown), second-degree atrioventricular block, ventricular extrasystoles, elevated blood pressure/hypertension (<1%), nausea/vomiting (1% to 10%), excessive drooling (<1%), elevated blood bilirubin (<1%), chills (1−10%), prolonged drug effect (frequency unknown).

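### Section 2.5 reads a negative result as little need to change practice, but with 45 per arm and no margin or smallest worthwhile effect a non-significant result cannot show that

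*Protocol*

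**What the plan says.** Section 2.5, on the significance of the study, closes with: "If the results are negative, it indicates that there is little need to change the current clinical practice". This is the only place where the protocol says what a negative result would mean.

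Section 9.2 sizes the trial. The propofol rate "was estimated to be 40% based on cases similar to our protocol", and "the relative risk of remimazolam to propofol for the frequency of hypotension associated with induction of anesthesia was reported to be 0.28". The enrolment target is 45 per group, 90 in total.

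Section 9.3.1.1 tests the primary outcome with a Mantel-Haenszel chi-square test stratified by ward hypertension. Section 9.3.1.2 adds a Mantel-Haenszel risk difference with a 95% confidence interval. No equivalence or non-inferiority margin is given, and no smallest reduction that would be worth having.

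Section 2.3 cites a less extreme relative effect from earlier work: 33% on remimazolam against 60% on propofol, for hypotension that needed treatment during general anesthesia.

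**The concern.** In a superiority trial, a p-value above 5% means that no difference was shown. It does not mean that no useful difference exists. To conclude that practice need not change, one must show that the data exclude a reduction worth having, and the protocol names no such reduction.

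The planning effect, a relative risk of 0.28, is very large. A trial sized on it can easily return a non-significant result when the true effect is smaller but still useful. Section 2.5 itself expects that fewer hypotensive episodes would improve care of the elderly and reduce costs, so a missed moderate benefit is the costly error. The sentence as written would present an imprecise result as an answer.

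**Working it through.** **Inputs.** Control rate 40%, relative risk 0.28, type I error 5% and power above 80% (section 9.2); 45 per arm (sections 6.2 and 9.2); cited rates 33% and 60% (section 2.3). Assumptions: a two-sided test, since sidedness is not stated, and no allowance for strata, since stratum rates are not given.

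**The plan's own figure.** The remimazolam rate is 0.28 × 40% = 11.2%, a difference of 28.8 points. The pooled formula is

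n = [1.96·√(2·p̄(1−p̄)) + 0.842·√(p₁(1−p₁) + p₂(1−p₂))]² / (p₁−p₂)²

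With p̄ = 0.256, n = (1.210 + 0.490)² / 0.288² = 34.8, so 35 per group. With continuity correction it is 42 per group, or 84 in total. Section 9.2 says "at least 84 participants per group would be needed"; the figure 84 reproduces only as a total. That is a separate wording error, and nothing below depends on it because 45 per arm is what will be enrolled.

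**Power at 45 per arm.** Each row sums the binomial probabilities of all outcome pairs that the test rejects at two-sided 5%. Mantel-Haenszel is without continuity correction.

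| True rates, propofol vs remimazolam | Basis | Mantel-Haenszel | Fisher |
|---|---|---|---|
| 40% vs 11.2% | planning effect | 90% | 85% |
| 40% vs 20% | risk halved | 55% | 46% |
| 40% vs 22% | relative risk 0.33/0.60 = 0.55 | 46% | 38% |
| 40% vs 18% | odds ratio of the cited rates | 64% | 56% |
| 60% vs 33% | cited rates as they stand | 72% | 65% |
| 40% vs 13% | cited 27-point difference | 84% | 78% |

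For the odds-ratio row: (0.33/0.67)/(0.60/0.40) = 0.328; 0.328 × (0.40/0.60) = 0.219; 0.219/1.219 = 0.18.

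An uncorrected Pearson chi-square test gives up to 86% in the last row, so the three scalings other than the relative risk span 56–86%.

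**Where 80% power ends.** Lowering the relative risk in steps of 0.01 at a 40% control rate, power first reaches 80% at 0.35 (Mantel-Haenszel) or 0.31 (Fisher).

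**Sensitivity to the control rate.** The 40% comes from one month of institutional data. With relative risk 0.55, Mantel-Haenszel power is 32% at a 30% control rate, 46% at 40% and 58% at 50%.

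**A result that section 2.5 would call negative.** Take 18/45 on propofol and 10/45 on remimazolam.
- Expected events per arm: 28 × 45/90 = 14. Variance: 28 × 62 × 45² / (90² × 89) = 4.876. Chi-square: (18 − 14)²/4.876 = 3.28, p = 0.07. Fisher gives p = 0.11.
- Risk difference: 22.2% − 40% = −17.8 points, 95% interval (Newcombe) −35 to +1.
- Relative risk: 0.222/0.400 = 0.56. The standard error of its logarithm is √(1/10 − 1/45 + 1/18 − 1/45) = 0.333, so the 95% interval is 0.29 to 1.07.

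The result is not significant, but the interval includes more than halving the risk.

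**The case against.** The sentence stands in a background section. No test, stopping decision or reporting commitment refers to it. Propofol is the standard, and keeping the standard when superiority is not shown is an ordinary default. Effect estimates with 95% intervals are already planned, so an imprecise null result would be visible as such. Every sample size depends on its assumed effect, and section 9.2 states that effect openly. These points limit the weight of the finding but do not remove it: the sentence remains the protocol's only reading of a negative result, and it claims more than such a result can show.

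Four stronger readings are tempting and are not supported.
- A reader might infer that the trial would usually miss the effect it cites. That holds only if the relative risk of 0.55 is moved to the 40% control rate. Section 9.2 treats 0.28 in that way, so the scenario is legitimate, but the other three scalings all give more than 50% power. In absolute terms the cited 27 points nearly equal the planned 28.8.
- A reader might set other remimazolam figures against the 40%. Section 10.3 lists "Major side effects: Hypotension 24.0% (36/150 cases" as an adverse-reaction rate, and the 67.7% in section 2.3 is for ASA class III or higher over a whole trial period. Neither is mean pressure below 65 mmHg up to 3 minutes after intubation, so neither makes a valid contrast. The 33% and 60% are also another endpoint and serve only as a plausibility check.
- A reader might say that a null result would count as support for propofol. The sentence says only that there is little need to change.
- A reader might say that 80% power holds only at a relative risk of 0.28. It extends to about 0.31 to 0.35.

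**Conclusion.** The point holds: a non-significant result from this design does not indicate little need to change practice. Power of 80% is confined to relative risks of about 0.35 or lower (0.31 with Fisher), and a true halving of the risk would be missed about 45% of the time with the planned test (100 − 55). For relative risk 0.55 at a 40% control rate the chance of a miss is about 54%, as one scenario and not the general case.

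These figures assume a 40% control rate, 45 evaluable patients per arm, two-sided 5% and no effect of stratification. Losses lower the power: at 42 per arm, relative risk 0.55 gives 44% (Mantel-Haenszel) or 35% (Fisher). The conclusion about section 2.5 does not rest on any single scenario. It rests on the lack of a named worthwhile reduction against which a null result could be judged. The defect is in the interpretation; the primary analysis itself is not affected.

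**What to change.** Replace the last sentence of section 2.5 with:

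*A non-significant result will be interpreted from the 95% confidence interval of the Mantel-Haenszel risk difference (section 9.3.1.2) and reported as inconclusive unless that interval excludes a reduction that the investigators name in advance as worthwhile.*

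The investigators must then state that reduction, in percentage points, before unblinding.

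Optionally, add to section 9.2 that with 45 per group and a 40% control rate, 80% power holds only for a relative risk of about 0.31 to 0.35 or smaller, depending on the test.

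The cost is a less definite statement about a null result and a power statement that looks less favourable away from the planning effect. No extra patients, measurements or analyses are needed.

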**3. Drug information**

**3.1. Trial drug**

**Product name:** Anerem

**Generic name:** Remimazolam besilate

**Manufacturing and sales company:** Mundipharma K.K.

**Indications:** Induction and management of general anesthesia

**Dosage and administration:** The dose for adult remimazolam is 12 mg/kg/hour by continuous intravenous infusion until loss of consciousness while monitoring the patient's condition.

**Drug form:** Injection drug (vial)

**3.2. Control drug**

**Generic name:** Propofol

**Indications:** Induction and management of general anesthesia

**Dosage and administration:** In adults, the drug should be administered intravenously at a rate of 0.05 mL/kg/10 s (0.5 mg/kg/10 s as propofol) while monitoring the patient's condition until loss of consciousness. In patients with ASA III or IV, it should be administered slowly. In adults, 0.20−0.25 mL/kg (2.0−2.5 mg/kg of propofol) is sufficient to achieve loss of consciousness. In the elderly, a smaller dose may be sufficient to achieve loss of consciousness.

**Dosage and administration for the elderly:** Because elderly patients often have liver, renal, or baroreceptor reflex dysfunction, side effects concerning cardiovascular are more likely to occur. This drug should be administered cautiously while observing the patient's condition (*e.g.*, slowing the administration rate at induction to 1/2, *i.e.*, approximately 0.025 mL/kg/10 s).

**Drug form:** Injection drug (vial or ample)

**4. Criteria and definitions used in this study**

Not applicable.

**5. Selection criteria for research participants**

**5.1. Inclusion criteria**

1. Patients aged ≥80 years who will undergo elective noncardiovascular surgery under general anesthesia
2. Patients who will be performed using rapid induction of general anesthesia with oral intubation
3. Patients who can communicate and obtain consent from the patient
4. Patients with an ASA physical status rating of class Ⅰ to Ⅲ

**5.2. Exclusion criteria**

1. Patients with a cerebral aneurysm or thoracic or abdominal aortic aneurysm
2. Patients with predicted or history of difficulty in airway management
3. Patients with drug allergies associated with this study
4. Patients on maintenance dialysis
5. Patients with severe liver dysfunction (*i.e.*, Child−Pugh class C)
6. Untreated and unstable ischemic heart disease
7. Severe aortic/mitral valvular disease
8. Arterial fibrillation or multiple premature atrial contractions or premature ventricular contractions
9. Congestive heart failure (*i.e.*, New York Heart Association classification Ⅲ or Ⅳ)
10. Pregnant women
11. Body mass index ≥30
12. Patients who regularly use antipsychotics or antidepressant drugs
13. Patients judged inappropriate for participation by researchers
14. Patients with mean blood pressure before induction of general anesthesia less than 70 mmHg*
15. Patients who failed the first attempt of tracheal intubation*

*Even after enrollment, it will not be included in the dropout or discontinuation but will be treated as an excluded case.

**6. Research plan**

**6.1. Design**

This is a single-center, double-blind, randomized, two-arm parallel-group, standard treatment-controlled, interventional clinical study.

**6.2. Sample size**

Ninety cases (standard treatment group: 45 cases and trial drug group: 45 cases)

**6.3. Study period**

**Study period:** From the date of approval for implementation until March 31, 2025

**Registration period:** From the date of approval for implementation until September 30, 2022

**Follow-up period:** Up to the day after surgery for each case

**6.4.2. Facility registration**

Not applicable (single-center study).

**6.4.3. Enrollment and allocation**

- 1. Blinded researchers will screen potentially eligible participants from the list of operations up to 1-day before surgery. Participants will be checked for inclusion and exclusion criteria.
  2. The principal investigator or subinvestigators fill out the case registration form. All participants will be identified by individual registry numbers used to anonymize the care report form or other documents. This individual registry number consists of numbers or letters not related to information that can identify a specific individual.
  3. Submit the case registration form to the registration center. The registration center checks the case registration form, and if eligibility is reconfirmed, proceeds to allocation.
  4. The **unblinded physician** determined the trial drug from the allocation sequence list. An **unblinded physician** is defined as one who is not consistently involved in patient recruitment, data collection, or anesthesia management during the study period, but only in drug administration.
  5. The research office will archive the registration confirmation form.

**6.4.5. Blinding**

In this study, unblinded researchers were responsible for the preparation and administration of the trial drugs. Trial drugs (*i.e.*, propofol or remimazolam) will be prepared before starting anesthesia on the day of surgery. This unblinded researcher will be dedicated to allocation, drug preparation, and administration and will not participate in other tasks such as recruitment, data collection, an anesthetist in charge, or an evaluator.

The syringe pump with trial drugs, covered with an opaque plastic bag, will be brought to the operating room by an unblinded researcher. After the participant will be laid on the bed, the syringe pump with a trial drug, IV line, and puncture site of the IV line of the participant’s forearm will be blinded to other researchers and the participant using towels, a partition, and opaque plastic sheets. After these procedures, another blinded researcher will enter the operating room and then will start the induction of general anesthesia.

**6.4.6. Unblinding procedures**

If serious adverse events (SAEs) such as a medical emergency, which requires identifying an intervention of individual participants, blinded investigators are permitted to inquire into unblinded investigators.

**6.5. Treatment plan**

**6.5.1. Protocol treatment**

**6.5.1.1. Trial drug group**

Remimazolam (12 mg/kg/h) will be continuously infused using a syringe pump until loss of consciousness, and then sevoflurane 1.5% will be started for maintenance of anesthesia. Three minutes after loss of consciousness, tracheal intubation was performed using a McGRATH MAC video laryngoscope.

**6.5.1.2. Control group**

Propofol (0.25 mg/kg/10 s) will be continuously infused using a syringe pump until loss of consciousness, and then sevoflurane 1.5% will be started as maintenance of anesthesia. Three minutes after loss of consciousness, tracheal intubation will be performed using a McGRATH MAC video laryngoscope.

**6.5.2. Concomitant medication and therapy**

**6.5.2.1. Concomitant medication and therapy**

**Remifentanil:** It will start at 0.25 mcg/kg/min before administering the trial or control drug. After tracheal intubation, remifentanil will be immediately decelerated to 0.05 mcg/kg/h.

**Rocuronium:** Rocuronium (0.6 mg/kg) will be administered after confirming loss of consciousness.

**Sevoflurane:** After confirming the loss of consciousness, sevoflurane 1.5% will be administered as a maintenance dose.

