**7.2.5. From the success of intubation to 3 minutes after intubation**

(1) Vital signs

Blood pressure and heart rate will be measured at 1-min intervals.

(2) Drug dose for induction of anesthesia

The number or dose of using any type of vasopressor between the start of sedative administration and 3 min after tracheal intubation

The dose of the trial drug for induction

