**8. Outcomes**

**8.1. Primary outcome**

The primary outcome will be the incidence of hypotension between the start of propofol or remimazolam and 3 min after tracheal intubation. The definition of hypotension is an MBP <65 mmHg measured by NIBP.

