**8.2. Secondary outcome**

- - 1. Maximum MBP 3 min after tracheal intubation
    2. Minimum heart rate after loss of consciousness.
    3. The number or dose of any type of vasopressor between the start of sedative administration and 3 min after tracheal intubation
    4. The time from the start of sedative drug administration to loss of consciousness. The loss of consciousness is defined as the loss of both the response to verbal stimuli and the reflex of the eyelashes. Loss of response to verbal stimuli was confirmed by calling his/her name every 10 s from the start of sedative drug administration.
    5. The dose of drugs used for anesthesia induction (*i.e.*, propofol or remimazolam)
    6. Incidence of injection pain. Participants will be asked a question about pain on injection after the start of sedative drug administration.

Pain on injection will be estimated by the following four-point scale:

0 = no pain

1 = mild pain (pain reported only in response to questioning and without any behavioral signs)

2 = moderate pain (pain reported in response to questioning and accompanied by a behavioral sign, or pain reported spontaneously without questioning)

3 = severe pain (strong vocal response or response accompanied by facial grimacing, drawing back the arm, or tears).

- - 1. Characteristics of the participants (age, sex, height, weight, medical history, comorbidity, medications [antihypertensive drugs, sleep-inducing drugs, antipsychotics, and central nervous system agents], ASA physical status, clinical frailty scale, surgery procedure, laboratory values of the latest surgery [hemoglobin, creatinine, and serum albumin]).
    2. Exploring factors associated with the incidence of hypotension

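### Remifentanil is started at a rate per minute but reduced after intubation to a rate per hour, a 300-fold drop as written where a 5-fold drop was probably meant

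*Protocol*

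**What the plan says.** Section 6.5.2.1 fixes the opioid background for both arms. On remifentanil it says: "It will start at 0.25 mcg/kg/min before administering the trial or control drug. After tracheal intubation, remifentanil will be immediately decelerated to 0.05 mcg/kg/h". No other section gives a remifentanil rate, says that the infusion is stopped, or explains the change of unit.

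The timing of the rate change relative to the outcomes follows from other sections:

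- Section 6.5.1.2 (control group): "Three minutes after loss of consciousness, tracheal intubation will be performed using a McGRATH MAC video laryngoscope". Section 6.5.1.1 sets the same interval for the remimazolam group.
- Section 8.1 defines the primary outcome as "the incidence of hypotension between the start of propofol or remimazolam and 3 min after tracheal intubation".
- Section 7.2.5, headed "From the success of intubation to 3 minutes after intubation", calls for blood pressure and heart rate every minute in that period.
- Section 8.2 lists as its first secondary outcome "Maximum MBP 3 min after tracheal intubation".

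**The concern.** One drug on one pump is given two time units in adjacent sentences. Taken literally, the second rate is so small that the infusion is effectively switched off. The verb used, decelerated, describes a slower running infusion, which fits a rate of 0.05 mcg/kg/min much better. So the hour is probably a slip for the minute.

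The new rate takes effect immediately after intubation, inside the primary-outcome window and at the start of the interval for maximum mean blood pressure. Vasopressor use is also counted to 3 minutes after intubation. If the rate is not correctly stated, the protocol does not define the opioid treatment under which those readings are taken, and another group could not reproduce it.

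There is a compliance side too. Section 13.1 bars departures from the protocol without prior approval, and section 13.2 requires each deviation to be recorded and reported. An anesthetist who gives 0.05 mcg/kg/min departs from the text; one who follows the text nearly stops the opioid. Section 9.1.2 counts breaches of the concomitant-therapy rules among the serious violations that remove a participant from the per-protocol set, so the doubt extends to that definition. Section 22.1 provides for self-inspection only, so no outside monitor would be there to notice inconsistent use.

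**Working it through.** **Inputs**

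- Starting rate: 0.25 mcg/kg/min (section 6.5.2.1).
- Rate after intubation, as printed: 0.05 mcg/kg/h (section 6.5.2.1).
- Time from intubation to the end of the primary-outcome window: 3 min (section 8.1).
- Body weight: not given in the protocol. A range of 45 to 60 kg is assumed, for illustration only.

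The protocol states no fold-reduction, so there is no figure of its own to reproduce.

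**Step 1. Common unit.** Starting rate: 0.25 × 60 = 15 mcg/kg/h. Later rate as printed: 0.05 / 60 = 0.00083 mcg/kg/min.

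**Step 2. Size of the reduction.**

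- As printed: 15 / 0.05 = 300-fold, to 0.05 / 15 = 0.33% of the starting rate.
- If both rates are per minute: 0.25 / 0.05 = 5-fold, to 20% of the starting rate.

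**Step 3. Amount delivered in the 3 minutes after intubation** (rate per minute × 3).

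| Reading | Rate (mcg/kg/min) | Amount over 3 min (mcg/kg) | At an assumed 45–60 kg (mcg) |
| --- | --- | --- | --- |
| As printed, per hour | 0.05 / 60 = 0.00083 | 0.0025 | 0.11–0.15 |
| Read as per minute | 0.05 | 0.15 | 6.8–9.0 |
| Starting rate unchanged, for comparison | 0.25 | 0.75 | 34–45 |

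The two readings of the later rate differ by 0.15 / 0.0025 = 60-fold. That ratio does not depend on the assumed weight.

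**Step 4. Share of the primary window affected.** Intubation comes 3 minutes after loss of consciousness. Before it, the window therefore contains the time to loss of consciousness plus 3 minutes, all at the undisputed 0.25 mcg/kg/min. After it come 3 minutes at the doubtful rate. The doubtful part is thus less than half of the primary window, but it is the whole of the post-intubation interval used for maximum mean blood pressure.

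These are pump settings and delivered amounts. The protocol gives nothing from which to derive plasma concentrations or effects on blood pressure, so none are estimated.

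**The case against.** The best case for leaving this as a minor drafting query has four parts.

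1. **It touches no inference.** The instruction is the same in both arms, and the anesthetists do not know the allocation, so they have no arm-specific reason to read it differently. No test, interval or sample-size figure depends on the rate. This stands, and it limits how much weight the point can bear.

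2. **The intended unit cannot be proved.** The printed rate is complete and can be set on a pump. The protocol also uses different time units elsewhere, with remimazolam in mg/kg/h and propofol in mg/kg/10 s. The first part stands: that this is a slip remains an inference. The comparison with the other drugs is weaker, because those are two different drugs, whereas here the unit changes within one drug between one sentence and the next.

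3. **The 300-fold figure describes a treatment that perhaps nobody meant to give.** That is fair as a comment on intent. But it is what the operative text tells staff to do, and a dosing instruction should not rely on readers to correct its unit. If near-cessation really was meant, the text still needs to say so, because the wording points the other way.

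4. **No effect on the outcomes is shown.** That is also true: no shift in hypotension incidence or in maximum blood pressure is estimated, nor could one be from this document. What is established is that the treatment condition for those readings is not properly defined.

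**Conclusion.** The point holds. The post-intubation remifentanil rate is given in a time unit that does not match the starting rate, and as printed it cuts the infusion 300-fold rather than 5-fold. The mismatch and the arithmetic are certain. That the hour should be a minute is probable, resting on the verb chosen, the unexplained switch of unit within one drug, and the plain 5-fold step that results.

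The consequence is limited but real: the opioid background is misstated or unclear for the final 3 minutes of the primary-outcome window and throughout the interval for maximum mean blood pressure after intubation. There is no between-arm bias from this source and no effect on type I error. Only the microgram amounts rest on the assumed 45–60 kg. It should be fixed because it is a live dosing instruction in patients aged 80 or over and the correction costs almost nothing.

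**What to change.** In section 6.5.2.1, change the post-intubation rate to 0.05 mcg/kg/min if that is what was intended. If near-cessation was intended, say so explicitly. In either case state both rates in the same time unit.

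If any participant has already been treated, confirm from the anesthesia records which rate was given, and report that rate with the results.

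The cost is a one-line protocol revision, submitted through the procedure in section 13.3.1. Design, sample size and analysis are unchanged.
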